## Abstract

**Background:**

Asbestos is the main cause of MPM in industrialized countries. Even since asbestos is banned in most developed countries, the peak wave of MPM incidence is anticipated for the next years due to the long latency of asbestos induced MPM. MPM patients not eligible for surgical procedures like decortication or pleuro-pneumectomie have a median survival of 12 months with palliative chemotherapy. Therefore, new therapeutic approaches are of crucial need in this clinical situation.

**Methods/design:**

This is a phase I trial for patients with malignant pleural mesothelioma with pleural effusion testing the safety of a fixed single dose of 1x10^6^ adoptively transferred FAP-specific re-directed T cells given directly in the pleural effusion. Lymphocytes will be taken 21 days before transfer from peripheral blood. CD8 positive T cells will be isolated and re-programmed by retroviral transfer of a chimeric antigen receptor recognizing FAP which serves as target structure in MPM. At day 0 of the protocol, re-directed T cells will be injected in the pleural effusion and patients will be monitored for 48h under intermediate care conditions. AE, SAE, SADR and SUSAR will be monitored for 35 days and evaluated by an independent safety board to define any dose limiting toxicity (DLT). No further patient can be treated before the previous patient passed day 14 after T cell transfer. The protocol will be judged as save when no DLT occurred in the first 3 patients, or 1 DLT in 6 patients. Secondary objectives are feasibility and immune monitoring.

**Discussion:**

Adoptive T cell transfer is a new and rapidly expanding branch of immunotherapies focusing on cancer treatment. Recently, objective responses could be observed in patients with chronic lymphatic leukemia treated with adoptively transferred CD19-specific re-directed T cells. The choice of the target antigen determines the possible on-target off-tissue toxicity of such approaches. There are reports of severe toxicity in patients who received T cells intravenously due to unexpected expression of the target antigen (on-target) in other tissues than the tumor (off-tissue). To minimize the risk of on-target off-tissue toxicity and to maximize the on-target anti-tumor effect we propose a clinical protocol with loco-regional administration of re-directed T cells. FAP-specific T cells will be directly injected in the pleural effusion of patients with MPM.

**Trial registration:**

ClinicalTrials.gov (NCT01722149)

## Background

### Malignant pleural mesothelioma

The worldwide incidence of malignant pleural mesothelioma (MPM) is still increasing due to the use of asbestos with regional differences ranging from 7 per million (Japan) to 40 per million (Australia) inhabitants per year [1]. In Europe, the annual incidence is about 20 per million inhabitants. Even since asbestos is banned in the industrialized world, it is still widely utilized in developing countries. Therefore, a wave of new cases is predicted in developing countries, for example in India [2].

Even when MPM is diagnosed at limited stage and in patients with good performance status, MPM is an incurable cancer despite the sequential use of different treatment modalities. Neither surgery nor radiotherapy alone has resulted in increased survival [3]. The survival of treated patients has a median of less than 12 months after diagnosis. Recently, the median survival could be improved by the sequential use of neo-adjuvant chemotherapy, extensive thoracic surgery including pleuro-pneumectomie and adjuvant radiation therapy [4-6]. However, the median survival is still not exceeding more than 2 years after diagnosis. Since the multi-modal approach is not evaluated prospectively so far, the impact of surgery on MPM is still debated [7]. Ultimately, there are attempts to prospectively test the role of surgery [8]. The European Organization for Research and Treatment of Cancer (EORTC) performed a retrospective analysis to identify prognostic factors. Important factors in MPM patients were histological subtype, performance status, and disease stage at time of diagnosis [9].

### Immunotherapy

Due to the unacceptable poor prognosis of MPM patients, new therapeutic approaches have to be developed. Immunotherapy is an attractive approach to add to current therapeutic concepts. Adoptive T cell transfer as part of immunotherapy is already used in clinical trials [10]. The main focus so far has been on the treatment of malignant melanoma due to the fact that melanoma antigens are known to be specific for the respective tumor cells. These so-called tumor-associated antigens (TAA) are the target structure to guide adoptively transferred T cells to the tumor. Over the last years, more and more TAAs became known in other cancer types [11,12]. However, the tumor consists not only of cancer cells but also of tumor stroma which includes fibroblasts, blood vessels, lymph vessels, and extracellular matrix proteins [13]. The tumor stroma itself appears to be a potential target for immunotherapy due to the over-expression of certain proteins that can act as target structures. Fibroblast activation protein (FAP) is such a target structure expressed by activated fibroblast in about 90% of all epithelial cancers [14]. We could identify FAP expression in all MPM subtypes (Figure 1). However, one major road block for the induction of TAA-specific T cells is the restricted T cell repertoire. Since the majority of tumor-antigens are self-antigens, no reactive T cell clones are present to recognize the cancer cells as they are deleted in the thymus [15].

**Figure 1 F1:**
[figure not shown]
**For the evaluation of the expression of FAP in MPM immunofluorescence (IF) microscopy was performed with the F19 antibody (A, C) or an irrelevant anti-CD20 antibody only (B, D).** Epithelioid (**A**, **B**) and sarcomatoid (**C**, **D**) MPM were analyzed. FAP staining is depicted in green. Cell nuclei were stained with DAPI (blue).

### Re-directed T cells

The generation of re-directed T cells may overcome this road block of a restricted T cell repertoire as shown by objective responses in patients with chronic lymphatic leukemia treated with CD19-specific re-directed T cells [16]. Re-directed T cells harbor a chimeric antigen receptor (CAR) that allows for the recognition of tumor-antigens and, therefore, leads to the activation of T cells independently of their original specificity (Figure 2) [17]. Recently, we reported the *in vitro* and *in vivo* activity of re-directed T cells targeting NY-ESO-1 positive and HLA2 positive tumors [18]. In parallel, we developed fibroblast activation protein (FAP)-specific re-directed T cells containing an immunoreceptor coding for the scFv recognizing (F19) linked to an IgG-spacer-domain, the CD28 co-stimulatory domain and the CD3ζ chain (Figure 2). Re-directed FAP-specific CD8+ T cells showed antigen-specific functionality in vitro and were protective in a xengraft model (manuscript under review). T cells will be re-directed by gene transfer *ex vivo* under GMP conditions. The CAR will be transferred into the T cells by retroviral transduction using the pBullet vector system that has already proven its safe use with re-directed T cells in clinical trials [19]. The preparation of the transgene-containing retrovirus supernatant met the quality and safety control criteria [20]. There were no descriptions of any secondary malignancy. However, recently an immune response against the vector system could be detected [21]. To target FAP, we will use the single-chain fragment of the humanised F19 antibody. The murine F19 antibody and a humanized version (sibrotuzumab) have already been used in two phase I trials with 17 patients [22] and 26 patients [23], respectively, and one phase II trial with 25 patients [24]. The biodistribution profile of the radio-labelled antibody in the phase I trial showed specific accumulation in FAP-positive hepatic metastasis of patients with colorectal cancer. No toxicity was observed in this trial [22]. The other trial was designed to identify the maximum tolerated dose. 218 doses were given and only one episode of dose-limiting toxicity was observed. The maximal tolerated dose was not reached. The one dose-limiting toxicity was back pain [23]. In the other phase II trial, 5 patients showed drug toxicity including rigors/chills, nausea, flushing and one incidence of bronchospasm [24].

**Figure 2 F2:**
[figure not shown]
**The chimeric antigen receptor F19 is a fusion protein which consists of four functional domains.** The scFv F19 serves as binding domain and binds to FAP. The IgG Fc-domain functions as a spacer (hinge); the CD28 signalling domain leads to co-stimulation and the CD3ζ signalling domain activates the T cell if the receptor is cross-linked via antigen binding. The CAR will be expressed in CD8 positive T cells with unknown endogenous specificity.

## Methods/design

### General study design

This is a phase I trial for patients with malignant pleural mesothelioma. A fixed single dose of adoptively transferred FAP-specific re-directed T cells will be given in the pleural effusion (Figure 3). Patients are eligible for the trial based on the inclusion and exclusion criteria presented in Tables 1 and 2.

**Figure 3 F3:**
[figure not shown]
**(A) Adoptive transfer of re-directed T cells: (1) 250 ml blood withdrawal at day −21, (2) separation of CD8+ T cells, (3) retroviral transduction of the CAR (+) specific for FAP, (4) adoptive transfer of re-directed T cells day 0. **(**B**) Study course: As concomitant palliative therapy chemotherapy with cycles of 21 days will be given before and after adoptive transfer. Re-directed T cells will be given 14 days after third cycle of palliative chemotherapy into the pleural effusion. Blood draw of 250 ml blood will be performed at day −21 for the production or re-directed T cells. Patients will be continuously monitored at an intermediate care unit (ICU) for the first 48h after the adoptive transfer of re-directed T cells into the pleural effusion (day 0). 30 min before the application of the re-directed T cells 16 mg Dexamethason will be given i.v. as pre-medication. The fourth cycle of palliative chemotherapy will be started 14 days after transfer. Palliative chemotherapy is not part of the study protocol. Radiation therapy is not permitted. Pleurodesis is not allowed until completion of the study. Supportive or other palliative measures are permitted without any exceptions. (**C**) CT scan of the thorax of a patient with MPM. The tumor nodules are attached to the pleural causing pleural effusion. The schematic syringe represents the application of the re-directed T cells in the pleural infusion resulting in a proximity of re-directed T cells and tumor.

**Table 1 T1:** Inclusion criteria

**Patients fulfilling all of the following inclusion criteria may be enrolled in the study**	
Inclusion criteria:	
· Histologically or cytologically confirmed and documented malignant pleural mesothelioma with pleural effusion,	
· Male and Female patients 18 years to 75 years of age,	
· Signed Informed Consent after being informed,	
· Patients medically and/or functionally at screening not accessible for surgical treatment with planned third cycle of palliative chemotherapy in 21 days,	
· Bone marrow function: hemoglobin ≥ 100 g/L; white blood cell count (WBC) ≥ 3.0 x 10^9^/L; absolute neutrophile count (ANC) ≥ 1.5 x 10^9^/L; platelet count ≥ 100 x 10^9^/L,	
· Hepatic: aspartate transaminase (AST) and alanine transaminase (ALT) ≤ 2.5 times upper limit of normal (ULN)); bilirubin ≤ 1.5 x ULN,	
· Renal: creatinine ≤ 2 mg/dL and creatinine clearance ≥ 45 mL/min,	
· No concomitant treatment with systemic corticosteroids, or any other immunosuppressive agents,	
· The patient has received no major organ allograft,	
· HIV-negative,	
· HBV and HCV negative,	
· No uncontrolled bleeding disorder,	
· Patients of child-producing potential must agree to use contraception while enrolled in the study and for 24 months after the adoptive transfer.	

**Table 2 T2:** Exclusion criteria

**The presence of any one of the following exclusion criteria will lead to exclusion of the subject:**	
Exclusion criteria:	
· Contra-indications to the class of TpP, e.g. known hypersensitivity or allergy to the investigational product,	
· Contra-indications on ethical grounds,	
· Women who are pregnant or breast feeding,	
· Intention to become pregnant during the course of the study,	
· Lack of safe contraception:	
Safe contraception is defined as follows:	
Female and male subjects of childbearing potential, using and willing to continue using a medically reliable method of double barrier contraception for the entire study duration and the next 2 years, such as oral, injectable, or implantable contraceptives, or intrauterine contraceptive devices in combination with preservatives. Or subjects who are using any other method considered sufficiently reliable by the investigator in individual cases.	
Please note that subjects who are surgically sterilized/hysterectomized or post-menopausal for longer than 2 years are not considered as being of child bearing potential.	
· Known or suspected non-compliance, drug or alcohol abuse,	
· Patients with medical history of coronary heart disease (CHD), stroke or peripheral vascular disease (PVD),	
· Patients with medical history of autoimmune disease such as multiple sclerosis, lupus, rheumatoid arthritis, inflammatory bowel disease or small vessel vasculitis,	
· Regular intake of immune-modulating drugs,	
· Inability to follow the procedures of the study, e.g. due to language problems, psychological disorders, dementia or confusional state of the subject,	
· Participation in another study with investigational drug within the 30 days preceding and during the present study,	
· Previous enrolment into the current study,	
· Enrolment of the investigator, his/her family members, employees and other dependent persons.	

Three patients who are at the time point of screening not operable will be treated with re-directed T cells administered into the pleural effusion after completion of 3 cycles of palliative chemotherapy (Figure 3). In the case of one AE grade III/IV or one SAE - both judged to be treatment related by an independent safety monitoring board - the patient number will be expanded to 6 patients. The study will be stopped if one additional DLT occurs also judged to be treatment related.

Patients will be treated with 1x10^6^ re-directed FAP-specific T cells injected in the pleural effusion. The study ends 35 days after adoptive T cell transfer. Re-directed FAP-specific T cells will be administered at day 0 (day 14 of the third cycle of palliative chemotherapy). The study is designed to demonstrate safety of 1x10^6^ re-directed FAP-specific T cells. The next patient will be enrolled earliest, when the previous patient completed day +14 and the safety monitoring board has not declared any DLTs. The palliative chemotherapy is not part of the study protocol. Due to nature of the study only descriptive statistics will be applied. Means, medians, standard deviations and ranges will be provided for continuous outcomes, and frequencies will be reported for categorical data. The study is approved by the local ethical committee (Kantonale Ethikkommission) of Zurich (KEK-ZH-Nr. 2012/0106), listed at ClinicalTrials.gov (NCT01722149) and in accordance with the Declaration of Helsinki.

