### Study objectives

#### Primary objective

The primary objective is to test safety of a fixed single dose of adoptively transferred FAP-specific re-directed T cells in the pleural effusion. Therefore, all grade III/IV AEs and SAEs will be measured. For the safety assessment, grade III/IV AEs and SAEs will be collected until day +35. The primary safety variables are abnormalities that are judged to be treatment-related and dose limiting toxicity (DLT) by an independent safety monitoring board after the patient passed day +35. Incidence and severity of treatment-related laboratory abnormalities, graded according to National Cancer Institute Common Terminology Criteria for Adverse Events (NCI-CTCAE) version v4.03 criteria as grade III-IV. The protocol will be judged as save when no DLT occurred in the first 3 patients, or not more than 1 DLT in 6 patients.

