### Dose rationale

This study is designed to show safety of a single dose. Therefore, we do not plan for a dose escalation. We decided to take the lowest dose of re-directed T cell recommended for second generation (CD28 signaling domain) CARs targeting a so far not tested tumor related antigen (FAP) [25]. We will administer 1x 10^6^ re-directed T cells into the pleural effusion.

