The main advantage of the loco-regional application of re-directed T cells is the avoidance of immediate systemic side-effects, since the re-directed T cells will not be systemically distributed by blood flow as if administered intravenously. Intravenous application can lead to an interaction of FAP re-directed T cells with off-target tissue leading to immunological mediated toxicity [25]. On-target off-tissue toxicity has to be addressed as first goal. Due to the fact that FAP is expressed in chronically inflamed tissue [28,29], off-target toxicity has to be taken into consideration. Furthermore, FAP expression could be found in fibroatheromata [30]. Therefore, patients with a medical history of autoimmune diseases and/or coronary heart disease, stroke and peripheral vascular disease are excluded from the study. More related to the systemic delivery of T cells, massive cytokine release could be caused by adoptively transferred T cells. There is one report describing an adverse event resulting in the death of a patient after the adoptive transfer of ERBB2 specific re-directed T cells [31]. The cause of death could be partially explained by a cytokine storm. The here presented study is differently designed. Re-directed T cells will not be given intravenously; therefore, a rapid and uncontrolled systemic contact to FAP positive tissue is not likely [32]. The patients are not lympho-depleted by palliative chemotherapy; therefore, clonal competition for cytokines can still take place and lowers the activation of transferred re-directed T cells [33]. Nevertheless, re-directed T cells may expand and migrate outside the pleural effusion and cause in the acute phase anaphylaxis and ARDS within the first 48h. Later on, chronic inflammation can be induced at different sites. Since this trial is the first trial evaluating FAP-specific re-directed T cells in the pleural effusion, all enrolled patients will be treated with the lowest suggested number of cells [25] and monitored for the first 48h at an intermediate care unit.

With the herein presented trial we propose a clinical trial design to test the safety of pre-clinically evaluated FAP specific re-directed T cells for loco-regional intrapleural therapy in patients with MPM.

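### The expansion, stopping and 'safe' rules count DLTs without regard to severity, and the article contradicts itself on what follows a first DLT

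*Protocol article*

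**What the plan says.** The text following Table 2, under General study design, sets the cohort: "Three patients who are at the time point of screening not operable will be treated with re-directed T cells". It then gives the expansion trigger, "In the case of one AE grade III/IV or one SAE", and its consequence once the event is "judged to be treatment related by an independent safety monitoring board - the patient number will be expanded to 6 patients". The stopping rule follows: "The study will be stopped if one additional DLT occurs also judged to be treatment related".

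The Primary objective section calls the protocol safe if the first three patients have no DLT, "or not more than 1 DLT in 6 patients". The abstract gives the same verdict in nearly the same terms.

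Three statements govern timing:
- General study design: a further patient may be enrolled only once the preceding one has completed day +14 and provided the board has declared no DLT.
- Abstract: a further patient may be treated once the preceding one is past day 14. No DLT condition is attached.
- Primary objective: grade III/IV AEs and SAEs are collected to day +35, and the board's judgement of DLT comes after that day.

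The Dose rationale fixes a single dose level: "Therefore, we do not plan for a dose escalation". On severe risk, the Discussion says of another re-directed T cell product: "There is one report describing an adverse event resulting in the death of a patient". It also names anaphylaxis and ARDS as possible in the present trial.

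**The concern.** The article defines neither SAE nor DLT, and grade V is not mentioned. A death therefore enters the expansion rule only as an SAE, where it has the same effect as a grade III laboratory abnormality. The stopping rule and the 'safe' verdict have no severity term either. With one dose level, the expansion patients receive the same exposure as the patient who had the event.

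Two things are at stake. The primary conclusion could read 'safe' with one treatment-related death among six patients. And after a first DLT the safety board would find instructions in the article that cannot all be followed.

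**Working it through.** **Inputs.** Cohort of 3, expansion to 6, and stop at a second treatment-related DLT (text after Table 2). 'Safe' at 0 DLT in 3 or at most 1 in 6 (Primary objective; Abstract). Gate at day +14 (General study design; Abstract). DLT judged after day +35 (Primary objective). Blood draw at day −21 (Figure 3 legend). The article states no target DLT rate and no operating characteristics, so there is no planned figure to reproduce. The true DLT rate p is an assumption, shown at 10%, 20% and 30%. Patients are taken as independent with a common p, and a treatment-related death is taken to be an SAE and a DLT.

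**Step 1: the count rule alone.** If patient 1 has a DLT, fatal or not, 'safe' requires no DLT in the next five patients:

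P(safe | DLT in patient 1) = (1 − p)^5

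Overall, 'safe' is reached with 0 of 3, or with exactly 1 of the first 3 and none of the next 3:

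P(safe) = (1 − p)^3 + 3p(1 − p)^5

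**Step 2: the General study design gate taken literally.** If every DLT is declared before the next enrolment, accrual ends at the first one. Six patients are never reached, P(safe | DLT in patient 1) = 0, and only the 0-in-3 route remains: P(safe) = (1 − p)^3.

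| Assumed p | Count rule: P(safe given DLT in patient 1) | Count rule: P(safe) | Literal gate: P(safe) |
|---|---|---|---|
| 10% | 0.9^5 = 0.590 | 0.729 + 0.3 × 0.590 = 0.906 | 0.729 |
| 20% | 0.8^5 = 0.328 | 0.512 + 0.6 × 0.328 = 0.709 | 0.512 |
| 30% | 0.7^5 = 0.168 | 0.343 + 0.9 × 0.168 = 0.494 | 0.343 |

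The two readings differ by 15 to 20 percentage points in the chance of a 'safe' verdict.

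**Step 3: the passages side by side.** After a first declared DLT, the text after Table 2 says to expand and the General study design gate says not to enrol. If the gate holds literally, the expansion and the 1-in-6 verdict can be reached only through a DLT not declared before the next enrolment. If the expansion is to have effect, the gate cannot mean what it says.

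**Step 4: timing.** The gate opens at day +14 and the judgement comes after day +35, so an event on days 15 to 35 can fall after the next enrolment. Whether it also falls after the next transfer depends on which gate applies. Under the abstract's gate, worded for treatment, it can. Under the General study design gate, worded for enrolment, a patient enrolled on day 14 whose blood is drawn that day is treated no earlier than day 14 + 21 = 35. That falls at the end of the window but can still precede the judgement. The gate says nothing about a patient already enrolled.

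**Step 5: what 1 in 6 can show.** The exact two-sided 95% CI has as its lower limit the 2.5% quantile of Beta(1, 6), 0.004, and as its upper limit the 97.5% quantile of Beta(2, 5), 0.641. That is 0.4% to 64.1%.

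**The case against.** The strongest reply is the enrolment gate. A reader of the expansion rule alone might infer that a treatment-related death in the first patient automatically leads to more enrolment. The article does not support that. Read literally, the General study design gate closes after a declared DLT, and a patient who dies before day +14 never completes day +14. The Discussion places the acute risks, anaphylaxis and ARDS, in the first 48 hours, well before the gate. An independent board also judges relatedness before any expansion. This much stands, and it limits the point.

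It does not remove the point. The gate treats a grade III DLT and a death before its day +14 limit alike, it contradicts the expansion it would have to govern, and the abstract omits its DLT condition. It is silent on the 'safe' verdict, and the board's stated task is to judge relatedness and DLT, not to weigh severity in the conclusion.

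Two further replies deserve weight. Rules of the 3-then-6 type commonly count DLTs without grading them, so counting alone is not an error. And a journal article condenses: the full protocol or the board's charter may define DLT and deal with fatal events. But the article does not leave this rule out. It states the expansion, stopping and verdict rules for its primary objective in full, and those statements conflict.

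Finally, the 59%, 33% and 17% concern any DLT in patient 1 under the count rule. They are not probabilities of a fatal outcome and do not say how likely the scenario is.

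**Conclusion.** The point holds in this form. The stated rules for expansion, stopping and the 'safe' conclusion have no severity term, so one treatment-related death in six patients is compatible with 'safe'. What follows a first DLT is contradictory: depending on the passage, the chance that a trial with a DLT in patient 1 ends 'safe' is either (1 − p)^5, that is 59%, 33% or 17% at p = 10%, 20% or 30%, or 0 if the DLT is declared before the next enrolment. The timing gap between day +14 and day +35 means that the gate does not reliably settle the matter.

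This rests on the assumptions that a treatment-related death is an SAE and a DLT, and that p lies in the range shown. It does not establish that the trial's full documents lack a provision for deaths, nor which clinical rule is right.

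**What to change.** Reconcile the Abstract, the text after Table 2, the General study design gate and the Primary objective on three matters: whether enrolment continues after a first DLT, whether the gate applies to enrolment or to transfer, and when the DLT is judged relative to that gate. State explicitly whether the count rule and the automatic 'safe' verdict apply when the DLT is fatal, and who decides. The clinical rule itself is for the sponsor and the safety board.

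Report any 1-in-6 result with the severity of the DLT and the exact 95% CI of 0.4% to 64.1%, so that 'safe' is not read as more than six patients can show.

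The cost is one paragraph, with no extra patients. The downside is that 'safe' may no longer follow automatically from the count.

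### The rule of no DLT in 3 patients, or at most 1 in 6, cannot support the stated conclusion that the dose has been shown to be safe

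*Protocol article*

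**What the plan says.** The aim is stated as a demonstration in two places. General study design (second paragraph after Table 2) says "The study is designed to demonstrate safety of" the fixed dose, and Dose rationale says "This study is designed to show safety of a single dose". Primary objective uses the milder idea of testing safety, but then fixes a verdict: the protocol will be "judged as save when no DLT occurred in the first 3 patients, or not more than 1 DLT in 6 patients". The abstract carries the same rule.

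The route to that verdict is in General study design (first paragraph after Table 2). It opens with "Three patients who are at the time point of screening not operable will be treated". After one grade III/IV AE or SAE that the board judges treatment related, "the patient number will be expanded to 6 patients". Then: "The study will be stopped if one additional DLT occurs also judged to be treatment related".

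The next paragraph adds a condition on enrolment: the previous patient must have passed day +14, and the board must not have declared a DLT. On analysis it says "Due to nature of the study only descriptive statistics will be applied", with frequencies for categorical outcomes. The article gives no tolerable or unacceptable DLT rate and no error rates for the rule.

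**The concern.** A rule based on 3 to 6 patients can screen out a very toxic dose. It cannot show that a dose is safe, because a favourable result is also likely when the true DLT rate is high. Here the favourable result is labelled in advance as a finding of safety, and that finding is the success criterion of the primary objective.

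The setting makes the label matter. There is one dose and no escalation, so no neighbouring dose adds information. The Discussion calls this the first trial of these cells in the pleural effusion and lists anaphylaxis, ARDS and later chronic inflammation as possible harms. It also says that the protocol is not meant to prove efficacy, but gives no matching caution for safety. A report that followed the plan to the letter would claim more than the data could show.

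**Working it through.** **Inputs from the article.** First stage of 3 patients; expansion to 6 after one event; stop at a second DLT; 'safe' if "no DLT occurred in the first 3 patients, or not more than 1 DLT in 6 patients". The article states no error rate, power or precision, so there is no figure of its own to reproduce.

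**Assumptions.** The true DLT rate p is not given, so 10% to 50% is shown. Patients are independent with a common p. The event that triggers expansion (treatment-related grade III/IV AE or SAE) is taken to be the same as a DLT.

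**Step 1: probability of the verdict 'safe'.** There are two favourable paths:

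- 0 DLT in 3: (1−p)³
- 1 DLT in the first 3, then 0 in the next 3: 3p(1−p)² × (1−p)³ = 3p(1−p)⁵

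P(safe) = (1−p)³ + 3p(1−p)⁵. At p = 1/3: (2/3)³ + 3 × (1/3) × (2/3)⁵ = 0.296 + 0.132 = 0.428.

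| True DLT rate | 0/3 path | 1/6 path | P(safe) |
|---|---|---|---|
| 10% | 0.729 | 0.177 | 0.91 |
| 20% | 0.512 | 0.197 | 0.71 |
| 30% | 0.343 | 0.151 | 0.49 |
| 33.3% | 0.296 | 0.132 | 0.43 |
| 40% | 0.216 | 0.093 | 0.31 |
| 50% | 0.125 | 0.047 | 0.17 |

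Solving P(safe) = 0.10 gives p of about 58%, and P(safe) = 0.05 gives about 66%. So the rule holds the risk of a wrong 'safe' to 5% only when about two patients in three would have a DLT.

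**Step 2: what a favourable result excludes (one-sided 95% upper bound).**

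- After 0/3: (1−p)³ = 0.05, so p = 1 − 0.05^(1/3) = 0.632, or 63%.
- After 1/6: the design reaches this only as 1/3 followed by 0/3, and 0/3 is the one more favourable outcome. The bound solves (1−p)³ + 3p(1−p)⁵ = 0.05, giving p = 0.656, about 66% (check: 0.0406 + 0.0094 = 0.0500).
- If n = 6 is treated as fixed, the Clopper-Pearson bound after 1/6 is 0.582, or 58%. This ignores the staging. Using 63% and 58% together misses the nominal level: just above p = 0.632 both favourable outcomes exclude the true rate, with probability 0.050 + 0.013 = 0.063.

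**Step 3: the enrolment condition.** Taken literally, no further patient may enter once the board has declared a DLT. A first DLT would then end recruitment, the 1/6 path could not occur, and P(safe) would be (1−p)³: 0.73 at 10%, 0.30 at one in three, 0.125 at 50%. This conflicts with the expansion to 6 in the paragraph before it and with the 1-in-6 branch in Primary objective. The bound after 0/3 stays at 63% under either reading.

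**The case against.** The best defence is that this is an ordinary 3+3-type rule in a small phase I trial. 'Safe' is then an operational label with its criterion printed beside it, tied to one stated dose. Primary objective speaks of testing safety, Dose rationale disclaims escalation, and the Discussion separates loco-regional from intravenous use. Much of this stands. The sample size and the rule are not at fault, and misuse of the result for other doses or routes is a possibility, not something the article invites. But the text goes beyond a label: it says twice that the design demonstrates or shows safety, and that is the claim the rule cannot bear.

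Three stronger readings are tempting, and the document does not support them:

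- A reader might infer that no confidence interval will be given. The restriction to descriptive statistics does not exclude an interval, and an analysis plan that is not shown may supply one, together with a target DLT rate.
- A reader might infer that means and standard deviations of three values will stand in for the individual data. Medians and ranges are promised too; with three patients, the median plus the minimum and maximum gives all three values. Nothing says that individual data will be withheld.
- A reader might take 43% as the design's error rate. One in three is an assumed benchmark. At a true rate of 10% the same rule says 'safe' 91% of the time.

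**Conclusion.** The concern holds as a mismatch between conclusion and design. A favourable outcome leaves DLT rates of up to 63% (0/3) or about 66% (1/6) unexcluded at the one-sided 95% level, and the verdict 'safe' has probability 0.49 at a true rate of 30% and 0.17 at 50%. The probabilities rest on an assumed range of DLT rates, on independent patients, on the expansion trigger being a DLT, and on expansion being allowed after a first DLT. The literal enrolment condition lowers the figure at one in three from 43% to 30%, and treating n = 6 as fixed lowers the second bound to 58%. Neither change makes the claim of safety tenable.

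This is a fault in the stated conclusion, not in the size of the trial. It should be corrected because it sits in the primary objective and correcting it costs almost nothing.

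**What to change.** - Keep the sample size and the decision rule. In General study design, Dose rationale, Primary objective and the abstract, replace the language of demonstrating, showing or judging safety with a limited conclusion, such as no DLT signal precluding further study at this dose.
- State the rule's operating characteristics over a range of true DLT rates, as in the table above.
- Report the DLT proportion with an exact 95% interval that accounts for the staged design, instead of one that treats 6 as a fixed sample size.
- Reconcile the expansion rule, the enrolment condition and the 1-in-6 branch, and say whether the event that triggers expansion is the same as a DLT. Which reading applies is for the sponsor and the safety board; the operating characteristics should then be computed for that reading.

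The cost is wording and one interval. The stated claim becomes less favourable. For this point no patient, visit or procedure changes.
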